# Neoadjuvant irradiation of extremity soft tissue sarcoma with ions (Extrem-ion): study protocol for a randomized phase II pilot trial

**DOI:** 10.1186/s12885-022-09560-x

**Published:** 2022-05-12

**Keywords:** Extremity soft tissue sarcoma, Carbon ion therapy, Proton therapy, Irradiation, Randomized trial, Hypofractionation, Heavy ion therapy

## Abstract

**Background:**

The standard of care treatment for soft tissue sarcoma of the extremities is a wide resection in combination with pre- or postoperative radiotherapy with high local control rates, sparing patients the necessity of amputation without compromising on overall survival rates.

The currently preferred timing of radiotherapy is under debate. Albeit having higher rates of acute wound complications, late side effects like fibrosis, joint stiffness or edema are less frequent in preoperative compared to postoperative radiotherapy. This can be explained in smaller treatment volumes and a lower dose in the preoperative setting. Particles allow better sparing of surrounding tissues at risk, and carbon ions additionally offer biologic advantages and are preferred in less radiosensitive tumors. Hypofractionation allows for a significantly shorter treatment duration.

**Methods:**

Extrem-ion is a prospective, randomized, monocentric phase II trial. Patients with resectable or marginally resectable, histologically confirmed soft tissue sarcoma of the extremities will be randomized between neoadjuvant proton or neoadjuvant carbon ion radiotherapy in active scanning beam application technique (39 Gy [relative biological effectiveness, RBE] in 13 fractions [5–6 fractions per week] in each arm). The primary objective is the proportion of therapies without wound healing disorder the first 120 days after surgery or discontinuation of treatment for any reason related to the treatment. The secondary endpoints of the study consist of local control, local progression-free survival, disease-free survival, overall survival, and quality of life.

**Discussion:**

The aim of this study is to confirm that hypofractionated, preoperative radiotherapy is safe and feasible. The potential for reduced toxicity by the utilization of particle therapy is the rational of this trial. A subsequent randomized phase III trial will compare the hypofractionated proton and carbon ion irradiation in regards to local control.

**Trial registration:**

ClinicalTrials.gov Identifier: NCT04946357; Retrospectively registered June 30, 2021.

## Background

Soft tissue sarcomas (STS) collectively account for approximately 1% of all adult malignancies [1]. There are more than 50 subtypes, while pleomorphic sarcoma, liposarcoma, leiomyosarcoma, synovial sarcoma, and malignant peripheral nerve sheath tumor account for 75% of STS [2]. With 43% the most common localization for STS are the extremities. Limb sparing wide resection in combination with radiotherapy (RT) is the current standard of care for high grade soft tissue sarcomas of the extremities [3]. Especially patients with G2/G3 sarcomas profit from the combination of RT and surgery [4]. Well-differentiated sarcomas (G1) receive no subsequent treatment after total resection (R0). Compared to amputation limb sparing resection with adjuvant RT shows similar overall survival (OS) und disease free survival (DFS) rates with a high local tumor control (LC) according to prospective studies [4–6] and a recent meta-analysis [7]. The status of postoperative resection margins is the most important prognostic factor contributing to LC with local recurrence (LR) being up to 3.76 times more likely in patients with positive compared to negative resection margins [8]. The sequence of surgery and RT is widely discussed by the radiation oncologists and surgeons. The main advantages of neoadjuvant (preoperative) radiotherapy are the smaller treatment target volumes and reduced prescribed radiation doses of 50 Gy vs. 66 Gy in 2 Gy single doses in the postoperative setting. Both preoperative and postoperative RT show a similar improvement in LC in prospective studies [4, 9–12]. In a recent retrospective study preoperative RT was predictive for R0 resection [13]. However, a greater incidence of acute wound complications was associated with preoperative compared to postoperative RT (35% vs.17%). Late-treatment–related side effects were more frequent in patients receiving postoperative RT, which could be explained by the higher RT dose and the larger treatment volume [10, 14]. The special physical and biological properties of protons and carbon ions lead to a superior dose distribution [15, 16]. This allows a better sparing of the surrounding tissue including the skin, muscles, joints, bones and subcutaneous fatty tissue, potentially reducing acute postoperative wound complications or late treatment related toxicities like fibrosis, joint stiffness, bone fracture or edema. Carbon ions are furthermore superior to protons based on their enhanced biological effectivity, which qualifies those for the treatment of tumors of low radiosensitivity as sarcomas. The standard neoadjuvant normofractionated radiotherapy consists of 25 fractions with 2-Gy single dose over 5 weeks; the special properties of particles allow hypofractionation resulting in a reduced treatment duration of less than 3 weeks.

This single-institution, prospective, randomized, open-label phase 2 trial evaluates the safety and feasibility of a hypofractionated, neoadjuvant proton or carbon ion radiotherapy based on the rate of wound healing disorders.

## Methods

### Primary objective

The primary objective of this trial is the evaluation of safety and feasibility of neoadjuvant hypofractionated irradiation in patients with extremity sarcoma using ions (protons or carbon ions) in raster scan technique. The primary endpoint is defined as the rate of wound healing disorders from beginning of radiotherapy to maximum 120 days after the planned tumor resection or discontinuation for any reason related to the treatment.

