### Toxicity, safety, and quality of life

Adverse events and toxicity will be reported according to International Common Terminology Criteria for Adverse Events (CTCAE) version 5.0 system. The results of clinical examinations as well as imaging studies (MRI or CT) will be included. Each patient will pass a baseline clinical examination after enrollment. Patients are monitored continuously during treatment, acute adverse events will be documented weekly as well as at the end of treatment. MRI of the according extremity will be planned 3 weeks and the resection 4–6 weeks after the end of radiotherapy. The first clinical follow-up presentation is 6 weeks after resection. Hereinafter all follow-ups include imaging studies and are performed 3, 6, 9, and 12 months after the tumor resection (Table 1). The criteria for feasibility and safety are fulfilled, if the rate of wound healing complications within 120 days after surgery is below 15% and if the therapy was not canceled, unless the reason for canceling is clearly not treatment related.

**Table 1 Tab1:** Time flow of procedures and examinations

	Study inclusion	Prior to RT	During RT	At the end of RT	3 wk. after RT	OP: 4-6 wk. after RT	6 wk. after RT	3 mo. after OP	6 mo. after OP	9 mo. after OP	12 mo. after OP
Inclusion and exclusion criteria	x										
Informed consent	x										
Medical history	x		x	x	x		x	x	x	x	x
Evaluation of symptoms and toxicity	x		x	x	x		x	x	x	x	x
Radiotherapy			x								
Resection						x					
MRI extremities		x			x			x	x	x	x
CT Thorax		x						x	x	x	x
Quality of life (QLQ-C30)		x			x			x			x

Quality of life (QoL) will be assessed by EORTC QLQ-C30 questionnaires. Repetitive completion of the forms is scheduled before treatment, 3 weeks after the end of radiotherapy, 6 months after surgery, and at the end of the study 12 months after surgery. Statistical analysis will be performed after complete acquisition of data. Changes in QoL before and after radiotherapy and before and after surgery will be determined. The two arms of the study will be compared after the end of radiation and at the end of the whole study.

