### Statistical methods

This study is performed to deliver basic data for the neoadjuvant hypofractionated carbon ion or proton radiation treatment of patients with extremity soft tissue sarcoma by providing safety and toxicity data for the here presented treatment regimen. The framework of the safety and feasibility considerations is the current standard neoadjuvant normofractionated photon radiotherapy; it is considered as the historical cohort which served for the planning of this pilot study. The randomization will be performed as block randomization at a ratio of 1:1 aiming at equal group sizes by using a web-based randomization tool (randomizer.at).

Due to the pilot character of the trial, all analyses are performed descriptively and the results are to be interpreted accordingly. The primary endpoint is assessed separately in each of the two treatment groups by applying an optimal adaptive two-stage phase II-design with one interim analysis according to Kunzmann and Kieser [19]. This design is an adaptive variant of Simon’s design [20], where the sample size of stage two is chosen optimally based on the results of the interim analysis. It offers the possibility to prematurely terminate the study due to futility or early success at the timepoint of the interim analysis or allows data-driven recalculation of sample size for the second part of the study while adhering to the specified Type I and Type II error rates. The randomization will be performed as block randomization at a ratio of 1:1. After the interim analysis, dependent on the results, different sample sizes in both treatment arms may be required and the randomization ratio would then be adjusted accordingly. Under the null hypothesis, we would expect in both groups wound complications or dicontinuations to occur in ≥35% of the treated patients within 120 days after surgery, so the expected probability of patients with no wound complications and no discontinuation would be π ≤ 65% for both protons as well as carbon ions. Under the alternative hypothesis, we would expect less than 15% of the patients to have wound complications or discontinue therapy within 120 days after surgery with π ≥ 85% being the rate of patients without wound complications or discontinuation within 120 days after surgery.

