Given these probabilities of success for the alternative and null hypothesis for the protons and carbon ion group, a statistical power of 1-β = 0.80 and a one-sided Type I error rate α = 0.05 for each of the two comparisons, the expected sample size under the null hypothesis is 25.59 and under the alternative hypothesis it amounts to 29.97; the maximum sample size in this design is 52. The interim analysis is performed when the data of 21 patients are available and therefore this is the minimum sample size. The recalculated sample sizes for stage 2 in both treatment arms depend on the patient number with a treatment success (no wound complications and no discontinuation). These values as well as the boundaries for early stopping and the decision boundaries after stage two are calculated according to Kunzmann and Kieser [19] with program code supplied by the authors. The estimation of success rates in both study arms is performed by calculation of point estimators [21] and calculation of two-sided 95%-Clopper-Pearson-type confidence intervals that take the adaptive two-stage design into account [22].

Analysis of the secondary time-to-event endpoints LPFS, DFS, and OS will be performed by the Kaplan–Meier method, patients without event will be censored. The treatment groups are compared using the logrank test. Quality of life will be measured by the EORTC-QLQ30 questionnaire and assessed by presentation of mean, standard deviation, median, minimum, and maximum as well as application of a two-sample t test. For the secondary endpoint local control, absolute and relative frequencies are calculated for each treatment group together with two-sided 95% Agresti–Coull confidence intervals, and an unconditional fourfold table test will be applied for treatment group comparison. Adverse and serious adverse events will be listed, and absolute and relative frequencies will be calculated.

The primary analysis for the primary and secondary endpoints is based on the intention-to-treat set including all study patients fulfilling the inclusion/exclusion criteria and having been treated for at least 1 week. Additionally, a per-protocol analysis is performed as sensitivity analysis which is based on all patients who have received the treatment as planned and for whom the relevant data is available. Safety endpoints are evaluated for all study patients for which the treatment has started.

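### The article counts discontinuation in its primary endpoint by three different rules and opens the window at two different times, so the same patient can be scored a success or a failure

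*Protocol article*

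**What the plan says.** The protocol article describes the primary endpoint in four places.

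- **Abstract, Methods:** the proportion of therapies "without wound healing disorder the first 120 days after surgery or discontinuation of treatment for any reason related to the treatment". Discontinuation counts only if treatment-related, and the wound window is the period after surgery.
- **Primary objective:** wound healing disorders from the start of radiotherapy to "maximum 120 days after the planned tumor resection or discontinuation for any reason related to the treatment". Relatedness is again required, but the window opens at the start of radiotherapy.
- **Toxicity, safety, and quality of life:** feasibility and safety require a wound complication rate below 15% within 120 days after surgery, and are met only "if the therapy was not canceled, unless the reason for canceling is clearly not treatment related". An uncertain cause therefore counts against the therapy.
- **Statistical methods:** under the alternative, fewer than 15% of patients "have wound complications or discontinue therapy within 120 days after surgery". The success that is counted at the interim is "no wound complications and no discontinuation". Neither phrase carries a relatedness qualifier.

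The Statistical methods section makes this count decide early stopping, the stage 2 sample size and, if the arms then differ in size, the randomization ratio. The Background section calls the trial open-label.

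**The concern.** A single-arm test of 65% against 85% success needs one rule that says, for every patient, success or failure. Here the rule depends on which section is read. The differences concern patients whom a neoadjuvant trial can expect to meet: those who stop for a reason unconnected with treatment, those whose reason is unclear, and those with a wound problem that has gone by the time of resection.

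With 21 patients at the interim, one patient is 1/21 = 4.8 percentage points, against a gap of 20 points between the hypotheses. Because treatment is open, a relatedness rule that is still unsettled at the interim could be settled after outcomes are known.

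**Working it through.** **1. The wordings side by side.**

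| Patient | Abstract | Primary objective | Toxicity section | Statistical methods |
|---|---|---|---|---|
| Stops radiotherapy, clearly unrelated reason | not a failure | not a failure | not a failure | failure |
| Stops radiotherapy, cause uncertain | not established as a failure | not established as a failure | failure | failure |
| Wound disorder that resolves before resection | not counted | failure | not counted | not counted |
| Completes radiotherapy, never resected | not fixed | not fixed | not fixed | not fixed |

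The first three rows are contradictions. The fourth is a case that the wordings leave open.

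**2. The interim rule, from the plan's own figures.** Inputs from Statistical methods: success 0.65 (null) and 0.85 (alternative), one-sided α 0.05, power 0.80, interim at 21 patients (read per arm, as each arm is assessed separately), expected sizes 25.59 and 29.97, maximum 52. The boundaries are not printed. A search over contiguous continuation regions of up to four counts found one that fits: continue at 16, 17 or 18 successes with 31, 17 or 9 further patients, stop for futility at 15 or fewer, and stop for success at 19 or more.

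E[N] = 21 + 31·P(16) + 17·P(17) + 9·P(18), with binomial probabilities for n = 21:

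- π = 0.65: 21 + 31(0.1085) + 17(0.0593) + 9(0.0245) = 25.59
- π = 0.85: 21 + 31(0.1147) + 17(0.1912) + 9(0.2408) = 29.97 (29.975 before the probabilities are rounded)
- Maximum: 21 + 31 = 52

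All three stated figures are reproduced.

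**3. How often one patient matters at the interim, at π = 0.85.**

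- Success to failure changes the decision at 16 (continue becomes futility) or 19 (early success becomes continue): 0.115 + 0.215 = 0.33.
- Failure to success changes it at 15 or 18: 0.054 + 0.241 = 0.295, about 29%.

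Both figures are conditional on a disputed patient being present.

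**4. Illustration of the effect on power.** The documents give no rate of disputed discontinuation, so 5% is an assumption, taken as independent of wound outcome. Counting these patients as failures gives 0.85 × 0.95 = 0.8075.

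The final cut-offs are not given. One set that fits requires 26 of 31, 14 of 17 or 7 of 9 stage 2 successes (totals 42, 31 and 25). Power is P(≥19) plus the sum of P(k) × P(stage 2 success given k) over k = 16, 17, 18:

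- π = 0.85: 0.3705 + 0.1147(0.683) + 0.1912(0.756) + 0.2408(0.859) = 0.80
- π = 0.8075: 0.2013 + 0.1758(0.434) + 0.2169(0.580) + 0.2022(0.758) = 0.56

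On these sample sizes, 78 cut-off sets meet α ≤ 0.05 and power ≥ 0.80. The same formula over all of them gives power of 0.80 to 0.88 at 0.85, and 0.56 to 0.69 at 0.8075. The value 0.56 is therefore the low end, from the set whose power at 0.85 is closest to the stated 0.80.

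**The case against.** **The wordings are closer than they look.** The Primary objective and Toxicity sections differ only for causes that cannot be judged, the Toxicity section states a feasibility criterion, and the Statistical methods wording may be shorthand for the endpoint already defined. This is fair, and it narrows the main conflict to clearly unrelated discontinuations. It does not remove it: the unqualified wording is the one attached to the hypotheses and to the count that triggers the interim decision.

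**The window differs little.** Every version ends 120 days after resection, so the start matters only for wound disorders that have gone before surgery. This stands as a limit on size. Likewise, a reader might infer that the Statistical methods wording cannot capture a radiotherapy stop at all, because resection follows radiotherapy by 4 to 6 weeks. That takes an upper time limit too literally.

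**Never-resected patients.** A reader might infer that such a patient counts as a success, having neither a surgical wound nor a discontinuation. The article does not say so. Resection is a scheduled procedure in Table 1, so its cancellation could equally be read as discontinuation and hence failure. Detailed scoring may also sit in the full protocol, which is not shown. What can be said is that these wordings do not fix it.

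**The trial is a descriptive pilot.** The Statistical methods section says so. But it also commits to specified error rates, early stopping and a recalculated sample size, all of which depend on this count. The objection lowers the urgency and does not remove the need for one definition.

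**Conclusion.** The point holds: the article contradicts itself on when discontinuation is a failure and on when the window opens, and the same patient can be scored both ways. It is a matter that should be fixed.

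Its size at the interim rests on boundaries inferred from the three stated sample sizes, which they reproduce. Given a disputed patient and π = 0.85, the decision changes with probability about 33% in one direction and 29% in the other. The power loss to about 0.56 rests on an assumed 5% rate and on one admissible cut-off set.

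Three stronger inferences are not supported.

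- **Adding the two directions to about 62%** mixes opposite reclassifications. A given patient can move only one way.
- **A rise in false success from 2.5% to 8.7%** when a 65% rate is read as 70% depends on a single one of the 78 cut-off sets. The stated α is 0.05, and the shift assumes that every disputed patient is free of wound complications.
- **That one patient always changes the outcome** is too strong. The count must lie at a boundary, and an arm moved from 19 to 18 recruits 9 more patients and still succeeds with probability about 0.86 at π = 0.85 under the cut-offs above.

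**What to change.** Use one endpoint definition in the abstract, the Primary objective, the Toxicity section and the Statistical methods section:

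- **One window:** from the start of radiotherapy to day 120 after resection.
- **One relatedness rule for discontinuation.** The Toxicity section's exemption, "unless the reason for canceling is clearly not treatment related", is a workable choice. Uncertain causes then count as failures and clearly unrelated ones do not.
- **The same rule for patients whose planned resection does not take place.** Do not add a second rule that fails all of them in the primary analysis, since this would conflict with the exemption. Add a sensitivity analysis that counts all unresected patients as failures.
- **Relatedness documented before each interim and final count,** so that it cannot be decided with the result in view.

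The cost is protocol wording and a short documentation step. Counting uncertain causes as failures gives a slightly less favourable success rate than the Primary objective wording would.

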### Secondary objectives

Secondary objectives include the assessment of local control (LC), local progression-free survival (LPFS) and disease-free survival (DFS). Overall survival (OS) will be calculated from the start of treatment until death or censoring. Quality of life (QoL) will be assessed using the EORTC-QLQ30 questionnaire.

### Study design

The study is a parallel-group, prospective, randomized clinical trial with an adaptive two-stage phase II trial design (including a sample size recalculation at the interim analysis) for patients with extremity soft tissue sarcoma, randomized to one of the two treatment arms (arm A: proton therapy, arm B: carbon ion therapy). The total dose of 39 Gy (RBE) in 13 fractions will be prescribed in both arms. The accrual period of this trial will take approximately 2 years with a follow-up time of 12 months for each patient. Patients meeting the eligibility criteria and willing to participate will give written informed consent and will be enrolled at Heidelberg University Hospital.

### Inclusion criteria

i)Histologically confirmed soft-tissue sarcoma of the extremities with an indication for perioperative radiation treatmentii)Resectable or marginally resectableiii)Karnofsky index of ≥70%iv)Age ≥ 18 yearsv)Carried out patient education and written consentvi)Patient is capable to give informed consent

### Exclusion criteria

i)Stage IV (distant metastases)ii)Lymph node metastasisiii)Metal implants that influence treatment planning with ionsiv)Previous radiotherapy in the treatment areav)Desmoid tumorsvi)Simultaneous participation in another clinical trial that could influence the results of the study.vii)Active medical implants for which no ion beam irradiation permit exists at the time of treatment (e.g., cardiac pacemaker, defibrillator)

### Treatment planning and target volume delineation

Examinations for treatment planning consist of a CT scan (3-mm slice thickness) in treatment position and an MRI for 3D image correlation. The delineation of the extremity soft tissue sarcoma requires a T1-weighted post-gadolinium sequence.

Before performing the planning CT the prospective location of incision for the surgery is marked by the surgeon and subsequently in the contrast enhanced CT represented by a steel wire in order to spare this region in the treatment planning if possible.

Gross tumor volume (GTV) consists of the gross tumor based on CT and MRI imaging. The clinical target volume (CTV) covers the surrounding areas at risk for containing microscopic disease. The CTV includes the GTV with a lateral margin of 1-2 cm and a longitudinal margin of 3-4 cm. CTV extension is limited to the anatomical compartments and includes the tumor surrounding edema. The planning target volume (PTV) includes the CTV with an additional margin of 7 mm in beam direction and 5 mm in all other directions (Fig. 1).

